**ETHICS COMMITTEE**

**APPLICATION TO CONDUCT A STUDY INVOLVING HUMAN SUBJECTS**

This form should be completed, signed by the Principal Investigator and Head of Department, and returned to [name], Personal Assistant to the Dean, LSHTM, [name].

Name of Principal Investigator ......[name].....................................................

Appointment held ...Research fellow................... Date ..........1.11.99...........................

Other Personnel involved............[name]..............................................

Title of project ........Studies on combination therapy with artesunate to delay the selection of resistance to antimalarial drugs in Pakistan...................................

..............................................................................................................

..............................................................................................................

I approve this project scientifically.

.............................................

(Signature of Head of Department)

Date ................................

Received by Ethics Committee

.............................................

.............................................

1. Give an outline of the proposed project. Sufficient detail of the protocol must be given to allow the Committee to make an informed decision. (Attach a summary of the project if this is more convenient).

Objectives:

To quantify the benefit of adding an artemisinin derivative to existing therapies with chloroquine and sulfadoxine-pyrimethamine in Pakistan. To compare this in randomized controlled trials against the currently recommended gametocytical and schizontocidal treatment of chloroquine plus primaquine. This will be assessed using the following indicators and end points: cure rate (elimination of parasitaemia without recrudescence), rate and time of parasite clearance, rate of resolution of fever, proportion of gametocyte carriers, transmissibility of gametocytes through mosquito feeding studies, tolerability, molecular characterisation of genetic diversity and resistance before and after treatment selection.

Rationale:

The increase in falciparum malaria in Pakistan over the last 15 years coincides with the spread of chloroquine resistance, which is now ubiquitous (Shah et al. 1997). We have reached the stage where chloroquine’s position as official first line treatment must be reconsidered. But in favour of what? Resistance to sulfadoxine-pyrimethamine (SP) stands at around 10% ([name] et al. 1997). If this drug was substituted as first-line, selection for SP resistance might follow the same pattern observed in SE Asia where use of SP had to be abandoned after just a few years. The Pakistani public is losing faith with the national drug policy and with government services (just as Afghan refugees are with UNHCR services), and are turning to the unregulated private sector where a wide range of antimalarials are sold ad hoc. Treatment policy has to change to avert a resistance catastrophe.

It is conceivable that chloroquine might still have a useful role. We know that extended treatment with chloroquine can overcome some R1 infections in Pakistan ([name], unpubl.). A drug with stronger trophozoitocidal activity (i.e. artesunate) might bring about that extra reduction in parasite load that enables the companion drug (chloroquine) to eliminate an otherwise R1 infection. We therefore propose to compare CQ (day 1,2,3) + AS (1,2,3) vs CQ (day 1,2,3).

If this combination fails it may be too late to preserve chloroquine in Pakistan (except for vivax treatment). Then it becomes even more crucial to preserve SP. The second comparison is therefore between SP (day 1) + placebo vs SP (day 1) + AS (day 1).

To improve our understanding of the genetic basis of drug resistance we will genotype parasites from blood samples of patients with treatment failure in this study. Blood samples of 20 patients from each arm of the study who had parasitological treatment failure will be selected randomly, together with midgut infections, and analysed for genetic markers of resistance to chloroquine and sulphadoxine/pyrimethamine.

4.2 Experimental design and methods:

Protocol design:

[[1]](#footnote-2)4bRandomised, double-blind, placebo control trial comparing (1) artesunate (AS) and chloroquine (CQ), vs CQ alone, vs CQ and primaquine (PR); (2) AS and sulphadoxine-pyrimethamine (S/P), vs S/P alone, vs S/P and PR.

Patients will be randomly assigned to one of the following treatment groups:

Adizai refugee camp in NWFP

- CQ (day1,2,3) + placebo (day 1, 3) vs
- CQ (day 1,2,3) + PR (day 1) + placebo (day 3) vs
- CQ (day 1,2,3) + PR (day 3) + placebo (day 1) vs
- CQ (day 1,2,3) + AS (day 1) + placebo (day 3)

Azakhel refugee camp in NWFP

- S/P (day 1) + placebo (day 1) vs
- S/P (day 1) + AS (day 1) vs
- S/P (day 1) + PR (day 1)

Sindh rural health centre

- CQ (day 1,2,3) + placebo (day 1,2,3) vs
- CQ (day 1,2,3) + AS (day 1,2,3)

Study sites - two areas with high malaria prevalence: Afghan refugee settlements in NWFP (Adizai and Azakhel) and Pakistani communities in Sindh province (Noshero Feroze).

Entry Criteria: adults or children > 5 yrs, weight > 5 kg, monoinfection with *P.faliciparum*, history of recent fever, consent from patient or parent. Exclusion: patients with signs of severe malaria.

Sample size calculation

Chloroquine combinations:

100 in each of the 6 study arms (assumes 5 % loss to follow up) = 400 cases will be recruited in NWFP (4 arms) and 200 in Sindh (2 arms). Assumptions for sample size (confidence level 95%, power 80%): 1. Estimated frequency of recrudescence in the chloroquine group: 30%, expected recrudescence in the test combination group: 10% or less. 2. Estimated prevalence of gametocyte positives after 7 days in the chloroquine group: 50%; in the test combination group: 25%.

S/P combinations:

150 in each of the 3 study arms = 450 cases will be recruited in NWFP. Assumptions for sample size (confidence level 95%, power 80%): 1. Estimated frequency of recrudescence in the S/P group: 10%, expected recrudescence in the test combination group: 1%. 2. Estimated prevalence of gametocyte positives after 7 days in the S/P group: 50%; in the test combination group: 25%.

Drugs and treatment regimens:

- AS dispensed as 50mg tablets at oral dose: 4mg/kg/day
- S/P dispensed orally as tablets (500 mg sulphadoxine and 25mg pyrimethamine)at oral dose: 25mg/kg based on sulphadoxine component, given once only
- CQ dispensed as 150mg base tablets at oral dose of base: 10mg/kg/day given once on day 0 & day 1, and 5mg/kg once on day 2.
- Primaquine will be dispensed as 7.5mg tablets at oral dose: 0.5mg/kg, given once only. All cases receiving primaquine will be screened for G6PD. Pregnant women excluded

Protocol operation:

Patients will be recruited by passive case detection from selected primary health care centres where diagnostic facilities or quality control are provided by HNI. In NWFP, two ARCs at Adizai (population 3,950) and Azakhel (population 16,248) in Peshawar and Nowshera districts will be the principal experimental sites. Each family is registered at the clinic which maintains family records. In Sindh, along the River Indus, a rural health centre in the most heavily affected district (Noshero Feroze) has been selected. This is presently being upgraded by HNI as part of our insecticide treated net project in the area. The catchment population is 30,000.

Subjects fulfilling the entry criteria will be medically screened: history, physical examination, malaria smear, and blood for Hb and/or PCV and white cell count. The 250 randomly-selected cases who will [[2]](#footnote-3)4creceive primaquine treatment will be screened for G6PD deficiency at admission, and cases positive for this condition will be closely observed over the next 48h for any adverse reaction i.e. haematuria. The recommended single dose of 0.5mg/kg primaquine is well tolerated (WHO, 1990) and it is standard practice to administer higher doses (primaquine for 5 days) for vivax treatment in Pakistan: no haemolytic reaction has been observed in G6PD deficient Afghans in previous studies ([name] & Durrani, 1999).

Patients will be allocated in equal numbers to each regimen using a supplied random number chart. Every antimalarial treatment will be administered by HNI health workers under supervision of a HNI licensed physician. The dose will be determined using supplied weight dosing charts. The same dose will be given again if vomiting occurs in first hour. Patients will return to the clinic 24 and 48 hours later for drug administration and for scheduled tests at 72 hours, days 7, 14, 21, 28, (and 42 for S/P arms). If a patient fails to report fieldworkers will locate him/her at his/her home address.

Follow up blood samples for haematology (Hb, PCV and WBC count) will be done using two different schedules: first 20% (see chant below): on days 0, 7 & 28. Remaining subjects: haematology on days 0 & 28.

| **Day** | **0** | **1** | **2** | **3** | **4** | **5** | **6** | **7** |  | **14** | **21** | **28** | **42** |
| --- | --- | --- | --- | --- | --- | --- | --- | --- | --- | --- | --- | --- | --- |
| History | X |  |  |  |  |  |  | X |  | X | X | X | X |
| Examination (clinical) | X | X | X | X1 |  |  |  | X |  | X | X | X | X |
| Temperature | X | X | X | X1 |  |  |  | X |  | X | X | X | X |
| Blood film | X | X | X | X1 |  |  |  | X |  | X | X | X | X |
| Filter paper PCR2 | X |  |  |  |  |  |  | X |  | X | X | X | X |
| Filter paper PK2 | X | X | X | X |  |  |  | X |  | X | X | X | X |
| Haematology | X |  |  |  |  |  |  | X |  |  |  | X | X |
| Thick & thin smears | X | X | X | X |  |  |  | X |  | X | X | X | X |

PCR/PK2 = A sample for PCR and for PK will also be obtained if the patient reports with clinical symptoms and a positive blood film at any time other than the above.

Thick and thin blood smears will be taken on days 0, 1, 2, 3, 7, 14, 21, 28, 42 (for S/P). Enrolment requires 5000 parasites/mm3.

A random selection of 20 patients (aged >13y) from each arm of the two studies in NWFP will be asked to volunteer for mosquito feeding studies on day 7 after treatment. The purpose of the study will be explained and written informed consent obtained. It is also hoped that up to 20 subjects (aged>20y) with recrudescent infections from each arm will also volunteer for feeding studies. Subjects will exposed to 30 unfed colony-mosquitoes (A.stephensi) reared in our insectary at Adizai ARC. Mosquitoes from single feeds will be kept in separate cages for 7 days and then dissected, oocysts counted, and midguts preserved for molecular genotyping at LSHTM using methods of Adagy and Warhust (1999) and Duraisingh et al. (1998).

| Activity | **Study Period (Months) Jul 2000 to Apr 2001** | | | | | | | | | | |
| --- | --- | --- | --- | --- | --- | --- | --- | --- | --- | --- | --- |
|  | **1** | | **2** | **3** | **4** | **5** | **6** | **8** | **7** | **9** | **10** |
| Initial planning and staff recruitment |  |  |  |  |  |  |  |  |  |  |  |
| Training of staff |  |  |  |  |  |  |  |  |  |  |  |
| Drug Trials |  |  |  |  |  |  |  |  |  |  |  |
| Data entry |  | |  |  |  |  |  |  |  |  |  |
| Data Analysis |  | |  |  |  |  |  |  |  |  |  |
| External coordinators/clinical monitors visits |  | |  |  |  |  |  |  |  |  |  |
| Preparation and submission of report |  | |  |  |  |  |  |  |  |  |  |

Reasons for discontinuation: severe malaria, as per the WHO definition, day 3 parasite count >=25%, parasitaemia present on day 7, recurrent parasitaemia, patient’s decision, consumption of a drug with antimalarial activity, haemolytic response to primaquine treatment.

Appropriate statistics will be used to analyse the results, as described in the full project document.

[[3]](#footnote-4)4d4.3 Ethical considerations

This clinical study will be conducted in accordance with the principles laid down by the World Health Assembly of 1975 on Ethics in Human Experimentation and the Helsinki Declaration. The study will adhere to the standards established for Good Clinical Practices (GCP) and conform to the TDR Standard Operating Procedures (SOP). The protocol of this study will be approved before it is initiated by LSHTM Ethical Committee. Written approval to perform this trial is being obtained from the Pakistan Medical Research Council.

If the field research is successful, genetic studies will be undertaken on the samples taken, and it would be hoped the project may be expanded in following years to cover other refugee camps to monitor any selection of drug resistance.

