4. State the likely duration of the project, and where it will be undertaken.

Will run from June 2000-April 2001 in the camps of Adizai and Azakhel in NWFP, and at a rural health centre in Sindh province, Pakistan.

5. Specify the procedures (including interviews) involving human subjects.

Subjects fulfilling the entry criteria will be medically screened: history, physical examination, malaria smear, and blood for Hb and/or PCV and white cell count. About 250 randomly-selected cases due to receive primaquine treatment will be screened for G6PD deficiency at admission. Every antimalarial treatment will be administered by HNI health workers under supervision of a HNI licensed physician using standard doses determined using weight dosing charts. Blood smears and samples for haematology (Hb, PCV and WBC count) will be done at intervals. Sample will be taken if the patient reports with clinical symptoms and a positive blood film at any time other than the above; radical treatment will be administered.

A random selection of 20 patients from each arm in NWFP will be asked to volunteer for mosquito feeding studies on day 7 after treatment. The purpose will be explained and written informed consent obtained. Subjects will exposed to 30 unfed colony-mosquitoes (A.stephensi) reared in our insectary at Adizai ARC.

6. State the potential hazards, if any, and the precautions being taken to meet them (include information on hazardous substances that will be used or produced, and the steps being taken to reduce risks).

The 250 cases due to receive primaquine treatment will be screened for G6PD deficiency at admission, and cases positive for this condition will be closely observed over the next 48h for any adverse reaction i.e. haematuria. Furthermore the recommended single dose of 0.5mg/kg primaquine is routinely administered without this attention and is well tolerated (WHO, 1990). It is standard practice to administer higher doses (primaquine for 5 days) for vivax treatment in Pakistan, and no haemolytic reaction has been observed in G6PD deficient Afghans in previous studies ([name] & Durrani, 1999).

7. State the procedures or activities which may cause discomfort or distress and the degree of discomfort or distress likely to be entailed by the subjects.

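### Early haematuria is sought more closely in G6PD-positive primaquine patients than in placebo or artesunate patients, so the tolerability comparison should use only data collected identically in all arms

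*Protocol*

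**What the plan says.** The Objectives (item 1 of the application) set the comparator: "To compare this in randomized controlled trials against the currently recommended gametocytical and schizontocidal treatment of chloroquine plus primaquine". The indicators and end points listed there include "tolerability, molecular characterisation of genetic diversity and resistance before and after treatment selection".

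G6PD testing is tied to the drug allocated. Drugs and treatment regimens says "All cases receiving primaquine will be screened for G6PD", and item 6, on hazards, says "The 250 cases due to receive primaquine treatment will be screened for G6PD deficiency at admission". For patients who test positive, Protocol operation in section 4.2 states that "cases positive for this condition will be closely observed over the next 48h for any adverse reaction i.e. haematuria". Neither the screening nor the observation is described for any arm without primaquine.

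The schedule common to all arms is also in Protocol operation. Every patient returns at 24, 48 and 72 hours. The table marks a clinical examination on days 0 to 3. It marks History on day 0 and not again until day 7, and it has no urine row. The accompanying text gives haematology on days 0, 7 and 28 to the first 20% of patients, and on days 0 and 28 to the rest.

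The reasons for discontinuation include "haemolytic response to primaquine treatment". One of the chloroquine arms is "CQ (day 1,2,3) + PR (day 3) + placebo (day 1) vs".

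**The concern.** In a randomised comparison of harms, each arm should have the same chance of having an event found. Here the allocated drug decides who is tested for G6PD deficiency and, through that test, who is watched for haematuria. A deficient patient on placebo or artesunate is neither identified nor watched. Blinding the assessors would not cure this, because the amount of looking itself differs between arms.

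Haematuria in the first days may come from the malaria episode, the background drug or the add-on drug. If it is found more readily after primaquine, part of any excess reflects the looking and not the drug. An analysis plan written later cannot recover events that were not sought in the comparator arms. The Rationale says that more research on primaquine is needed before the health ministry decides whether to drop it for artesunate, so the contrast could carry weight in policy.

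**Working it through.** **1. The plan's own count.** The application gives 250 primaquine recipients to be screened. The chloroquine trial has "100 in each of the 6 study arms (assumes 5 % loss to follow up" and two of those arms contain primaquine. The S/P trial has 150 per arm, and one arm contains primaquine.

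- By the listed arms: 100 + 100 + 150 = 350. The stated 250 is not reproduced.
- 250 results only if one of the two chloroquine plus primaquine arms is left out: 100 + 150.
- Comparators in the same randomisations: 100 (CQ + placebo) + 100 (CQ + AS) + 150 (S/P + placebo) + 150 (S/P + AS) = 500.

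**2. Who is actually watched.** Only the G6PD-positive among those screened. The documents give no prevalence, so take g = 2% to 15% as an assumption.

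- Watched, if all primaquine recipients are screened: 350 × 0.02 = 7 to 350 × 0.15 = 52.5.
- Deficient comparators who are not identified: 500 × 0.02 = 10 to 500 × 0.15 = 75.

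**3. What each deficient patient receives in the first three days.**

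| | Primaquine, G6PD-positive | Placebo or artesunate, G6PD-deficient |
|---|---|---|
| Deficiency known | yes | no |
| Clinical examination, days 1 to 3 | yes | yes |
| Scheduled history or urine item, days 1 to 3 | none | none |
| Close observation for haematuria, 48 h | yes | no |
| Haematology before day 7 after baseline | none | none |

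The last row but one is the only difference in ascertainment. Haematology does not fill the gap: 80% of patients have it only on days 0 and 28.

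**4. Size if the true risk is equal.** Let b be the true risk of haematuria in deficient patients, s1 the chance of detection under close observation, s0 the chance at the common visits, and r the risk in non-deficient patients, who are followed alike in all arms.

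- Recorded rate, primaquine: g·b·s1 + (1 − g)·r·s0
- Recorded rate, comparator: g·b·s0 + (1 − g)·r·s0
- Difference due to ascertainment alone: g·b·(s1 − s0), or g·b·(1 − s0) with s1 = 1

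All of g, b and s0 are assumptions. With g = 2% to 15%, b = 2% to 20% and s0 = 0 to 0.9, for the 100 + 150 = 250 patients given primaquine on day 1:

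| Case | g | b | s0 | Difference | Extra recorded cases in 250 |
|---|---|---|---|---|---|
| Smallest | 0.02 | 0.02 | 0.9 | 0.00004 (0.004 points) | 0.01 |
| Mid-range | 0.10 | 0.10 | 0.5 | 0.005 (0.5 points) | 1.25 |
| Largest, s0 = 0.5 | 0.15 | 0.20 | 0.5 | 0.015 (1.5 points) | 3.75 |
| Largest, s0 = 0 | 0.15 | 0.20 | 0 | 0.03 (3.0 points) | 7.5 |

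In the mid-range case with r = 1%, the recorded rates are 0.010 + 0.0045 = 1.45% and 0.005 + 0.0045 = 0.95%. The last row supposes that the examinations on days 1 to 3 find nothing, which is an extreme. If collection is identical, s1 = s0 and the difference is 0.

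**5. The day-3 primaquine arm.** Screening is at admission. The third treatment day falls at the 48 hour visit. If the 48 hours of observation run from admission, they end at about the time primaquine is given. The extra watching then mostly precedes exposure: it can add events that primaquine did not cause, and it can miss ones that it did. The formula above does not apply to these 100 patients.

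**The case against.** The close observation is a safety precaution, and item 6 presents it as one. Nothing says that its findings will enter a between-arm table. Tolerability is one entry in a list, the analysis is referred to a fuller project document, and conduct is to follow standard operating procedures that are not shown; an adverse-event question for all arms may be there. Every patient is examined on days 1, 2 and 3, and those who fail to report are traced. The protocol also says that no haemolytic reaction was seen in G6PD-deficient Afghans in previous studies, which, if it holds here, leaves few events to miscount.

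Most of this stands as to size. The daily examinations raise s0, and a low b shrinks the difference towards zero. It does not remove the mechanism: as written, the one haematuria-specific observation is confined to primaquine patients, and no matching item appears in the common schedule.

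Three stronger readings are tempting and are not supported.

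- A reader might infer that 350 patients are under active surveillance while 500 have none. Only the G6PD-positive are watched, and all 500 are examined on days 1 to 3.
- A reader might infer that haemolysis can be recorded only for a primaquine patient. The item naming primaquine is a reason for discontinuation, not a definition of what may be recorded, and haemoglobin is scheduled alike in all arms.
- A reader might attach a rate ratio of 1/s0, say 1/0.75 = 1.3 to 1/0.25 = 4.0. Those detection rates are not in the documents, and the ratio would apply to deficient patients only.

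**Conclusion.** The point holds in a limited form. The plan makes tolerability a randomised comparison and states unequal case-finding for one early harm. With equal true risk, haematuria in G6PD-deficient patients is more likely to be recorded in the arms given primaquine on day 1 than in the placebo or artesunate arms. The direction follows from the text, provided that close observation finds at least as much as a routine examination and that its findings are counted in the comparison.

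The size cannot be derived from the documents. It is confined to the G6PD-positive minority, is reduced by the examinations in all arms, and is probably small in absolute terms. It would be wrong to conclude that the tolerability comparison as a whole is tilted against primaquine: other symptoms and haematology are collected alike, and in the day-3 arm the direction is unclear. Severity is minor; the change is a cheap improvement.

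**What to change.** Leave the safety observation and the reasons for discontinuation as they stand, and change only what is recorded and compared.

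1. At the existing 24, 48 and 72 hour visits, put one structured question on dark urine or haematuria, in the same words, to patients in every arm and record the answer.
2. State that the between-arm tolerability comparison uses only data collected identically in all arms: that question, and haemoglobin change at the visits common to all. Report events found solely through the 48 hour observation descriptively for the primaquine arms.
3. Reconcile the day-3 primaquine arm in Protocol design with the 48 hour window in Protocol operation, and the 250 patients to be screened with the 350 primaquine recipients implied by the arm sizes.

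If the procedures not shown already contain such a question, only items 2 and 3 remain.

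The cost is one case-record field and a short protocol statement, with no added visit, test or patient. The downsides are a little more data entry and the loss of observation-only events from the comparative table. Two limits remain. Haemoglobin change for most patients spans day 0 to day 28 and says little about the first days. In the day-3 arm, only the 72 hour answer falls after primaquine and before the day 7 history.

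### Tolerability is a listed end point, but no history is scheduled at the 24, 48 and 72 hour visits, so the first symptom enquiry planned in all arms after treatment starts is on day 7

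*Protocol*

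**What the plan says.** The Objectives (item 1 of the application) include among the indicators and end points "rate of resolution of fever, proportion of gametocyte carriers, transmissibility of gametocytes through mosquito feeding studies, tolerability".

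The follow-up table in section 4.2, under Protocol operation, has columns for days 0 to 7, a blank column, and then days 14, 21, 28 and 42. Its first row reads "History | X | | | | | | | X | | X | X | X | X", which places history on days 0, 7, 14, 21, 28 and 42. The next row begins "Examination (clinical) | X | X | X | X1", so examination is marked on days 0 to 3, and temperature follows the same pattern.

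The text above the table confirms that patients are present on those days: "Patients will return to the clinic 24 and 48 hours later for drug administration and for scheduled tests at 72 hours". Anyone who does not attend is traced at home.

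On dosing, Drugs and treatment regimens describes chloroquine as "given once on day 0 & day 1, and 5mg/kg once on day 2", whereas the arm list under Protocol design numbers the same three doses 1, 2 and 3. S/P is given once, and its partner drug or placebo is given on the same day.

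Two drug-related observations are named before day 7. One is "The same dose will be given again if vomiting occurs in first hour". The other is close observation over 48 hours, for signs such as haematuria, of primaquine recipients found to be G6PD-deficient.

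**The concern.** The reactions that a tolerability comparison of oral antimalarials mainly turns on, such as nausea, later vomiting, dizziness, itching and abdominal pain, are reported by the patient and seldom found on examination. They would be expected during dosing and in the day or so after it. The schedule brings patients to staff three times in that window and records temperature, films and examination, but it provides for no history. A declared end point is thus left without a planned measurement at the time when it is most informative.

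At stake is how well the trial can describe and compare the tolerability of artesunate, primaquine and placebo when added to chloroquine or S/P. Enquiry about other drugs taken has the same gap: taking another antimalarial is a listed reason for discontinuation, yet no question about it is scheduled between day 0 and day 7.

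**Working it through.** No sample size or power figure bears on this point. The check is a reading of the schedule against the dosing days, plus a search for any other collection of symptoms.

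**1. Column reading**

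| | Day 0 | Day 1 | Day 2 | Day 3 | Day 7 |
|---|---|---|---|---|---|
| Patient seen | entry | 24 h | 48 h | 72 h | yes |
| History | X | – | – | – | X |
| Examination | X | X | X | X | X |
| Temperature | X | X | X | X | X |

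History is marked at 0 of the 3 visits on days 1 to 3, and examination at 3 of 3. Counting day 7 as well, history is marked at 1 of the 4 visits after day 0. The blanks do not look like a reading fault. Neighbouring rows fill days 1 to 3, and the Haematology row marks days 0, 7 and 28, as the text above the table also says, so the columns line up.

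The day-0 history belongs to the medical screening at entry. It can serve as a baseline but cannot capture reactions to the drugs.

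**2. Interval from dose to first history**

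Interval = 7 − day of the dose, on the schedule's numbering.

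- Three-day regimens, last dose on day 2 (regimen text): 7 − 2 = 5 days.
- Three-day regimens, with the arm list's day 3 read literally on the schedule: 7 − 3 = 4 days.
- S/P arms, all drugs at the first visit: 7 − 0 = 7 days.
- Adizai artesunate arm and first-day primaquine arm, partner drug at the first visit: 7 − 0 = 7 days from the partner drug.
- Adizai third-day primaquine arm, partner drug at the third visit: 7 − 2 = 5 days.

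The last two lines show that the two primaquine timings would be asked about at recall distances that differ by 7 − 5 = 2 days.

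**3. Patients affected**

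Chloroquine arms: 6 × 100 = 600. S/P arms: 3 × 150 = 450. Total: 600 + 450 = 1050 planned (item 3 of the application says about 1000). The missing history applies to all of them. Dosing over three visits applies only to the 600.

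**4. Other sources before day 7**

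- Vomiting in the first hour: covers one symptom for one hour, and is mentioned only as a reason to repeat the dose.
- 48-hour observation: limited to G6PD-deficient patients who receive primaquine.
- Unscheduled attendance: samples are taken when there are symptoms and a positive film, so it detects malaria rather than drug reactions.
- Haematology: does not record symptoms, and is not scheduled between day 0 and day 7.

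None is a symptom enquiry in all arms, and no adverse-event form or questionnaire is described.

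**The case against.** The strongest reply is that the protocol defines neither History nor Examination. A clinical examination is marked on days 1, 2 and 3, and treatment is given by health workers under a physician's supervision, so symptoms may well be asked about. The document is also an outline for an ethics committee. It says that the study will follow GCP and TDR operating procedures, and adverse-event recording may sit there or in the case record forms. This stands to the extent that a reader should not infer that nobody would ask about symptoms before day 7. It does not close the gap. The table and the entry-screening text both list history separately from examination, and questions that are neither scheduled nor standardised do not yield comparable data across arms. The general reference to operating procedures does not alter the schedule that the protocol itself fixes, and the full project document is cited only for the statistics.

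A second reply is that the trial is double-blind and the day-7 history falls on the same day in every arm. This also stands. A reader might infer that every arm would look equally well tolerated, or that any tolerability claim would be worthless. The documents do not support that: recall on day 7 lowers sensitivity and may shrink differences, but it does not erase them.

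Two further inferences should be resisted:

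- Days 1 to 3 are not the dosing window for everyone. In the 450 S/P patients all drugs are given at the first visit, and for them those days are the period just after the dose.
- Fever resolution is not left unmeasured. Temperature is taken on days 0, 1, 2, 3 and 7, which is an objective measure, and having recent fever as an entry criterion does not contradict it.

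Finally, the sample size rests on recrudescence and on gametocyte prevalence after 7 days, not on tolerability. That limits the weight of the point but does not remove it, since tolerability is a stated end point.

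**Conclusion.** The point holds in a limited form. The protocol names tolerability as an end point and schedules no history at three visits where patients are present and examined. Outside two narrow observations, no symptom enquiry in all arms is planned between day 0 and day 7. The resulting recall interval is about 4 to 5 days from the last dose in the three-day regimens and about 7 days from the only dose in the S/P arms. The likely effect is under-recording of short-lived reactions and some attenuation of differences between arms. Its size cannot be computed, because the document gives no expected symptom frequencies.

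This rests on two assumptions: that the schedule is followed as written, and that no case record form or operating procedure outside this document already requires a symptom list on days 1 to 3. If one does, the remedy is to say so in the schedule. The change is worth making, but the main efficacy comparisons do not depend on it.

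**What to change.** - Mark History on days 1, 2 and 3 in the schedule.
- At these visits and on day 7, ask one fixed symptom list in the same words in every arm, including vomiting since the last visit and other drugs taken.
- Record the answers, and report tolerability as symptoms new or worse than in the day-0 history.
- Reconcile the day numbering between the arm list (from day 1) and the regimen text and schedule (from day 0), so that each record can be placed relative to the dose.

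The cost is three marks in the table, a short checklist and a few minutes per visit. Patients already attend or are traced at home on these days, so no visit, blood sample or change to treatment is added.
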